### Randomisation

All patients diagnosed with an extra-articular AO type A1, A2 or A3 distal radius fractures will be requested to participate in this study. Patients will be eligible after adequate reduction of the fracture has been acquired. Upon obtaining informed consent, patients will be randomised into either the intervention group (ORIF with a volar locking plate) or the control group (closed reduction and plaster immobilisation). This will be performed online by randomisation software provided by the Clinical Research Unit of the Academic Medical Centre Amsterdam. In order to avoid any imbalances between treatment groups, patients will be randomised into three strata according to age: 18-30, 31-60 and >60 years using a block randomisation.

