### Secondary outcomes

• Rist pain and disability expressed as change on Patients-Rated Wrist Evaluation Score (PRWE). The PRWE is a validated tool for assessing functional outcome in patients with distal radius fractures [21]. This score was first described in 1998 by McDermid et al. [22] and developed by expert surveys. The PRWE is a 15-item questionnaire designed to measure wrist pain and disability in activities of daily living. The PRWE allows patients to rate their levels of wrist pain and disability from 0 to 10, and consists of three subscales: Pain, Function and Cosmetics.

• Quality of Life assessed using the Short Form–36 (SF-36^®^) questionnaire. The SF-36 is a validated multipurpose, short form health survey which contains 36 questions representing eight different health domains [23]. These domains are combined into a mental and physical component scale. From each domain, scores ranging from 0 to 100 points are derived, with lower scores indicating poorer quality of life.

• Pain as indicated on a visual Analogue Scale (VAS), in which 0 implies no pain and 10 the worst possible pain. Patients will be asked to give an estimation of the type and quantity of pain medication taken during all follow up visits.

• Patient satisfaction at one year by simply asking patients if they are satisfied with the result (yes/no).

• Range of motion of the wrist measured on both sides with a handheld goniometer.

• Prehensile grip strength as measured with a Baseline dynamometer.

• Radiological parameters: radial inclination, volar/dorsal tilt, communition, ulnar variance and radial length measured digitally in the Picture Archiving and Communication System (PACS) on standard posterior anterior (PA), lateral carporadial and lateral X-rays of the wrist. Radiographs will be obtained according to standardised procedures. PA radiographs with the shoulder in 90 degrees abduction, elbow in 90 degrees flexion and the wrist in neutral position; lateral X-rays with the shoulder in neutral position and elbow in 90 degrees flexion; and the lateral carporadial radiographs will be obtained by positioning the lower arm on a 20-25 degrees angled wedge.

• Rate of cross-overs

• Complications such as: loss of reduction, fracture malunion or non-union, wound and/or plate infection, tendon irritation and/or rupture, neuropathy and the occurrence of complex regional pain syndrome according to the criteria by Veldman et al. [24].

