### Sample size

This sample size calculation is based on the primary endpoint, the DASH score. The DASH score of an individual without any complaints of the wrist is 0. The mean DASH score after closed reduction and cast treatment after one year of follow up is 19 with a standard deviation (SD) of 18 [25]. This figure was measured in a patient population in which 72% suffered from a displaced extra-articular distal radius fracture. We assume that treatment with volar plating will decrease the DASH score which is achieved by conservative cast treatment by 15 points, from 19 to 4. Therefore at α = 0.05% and a power of 90%, with an estimated lost to follow-up of 10%, we would require 66 patients in total and 33 per treatment arm, to participate in the trial. This figure was calculated using the standard formula for means of superiority trials: n = [A + B]^2^ * 2 * SD^2^/DIFF^2^, where N = the number of patients required per arm, A the level of significance, B the power, SD the standard deviation of the primary outcome and DIFF the difference between the means. For safety measures and to correct for natural deaths, 45 patients in each arm will be included. From a separate study being conducted at the Academic Medical Centre Amsterdam and two other teaching hospitals, it was established that of the 703 distal radius fractures encountered in one year, 328 were an AO type A2 and A3. Therefore we estimate that we require a maximum of two years to include and follow up the patients in this trial.

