### Statistical analysis

Patients will be analysed according to the intention-to-treat protocol. General descriptive statistics on patient characteristic at baseline will be performed including factors such as gender and age. The primary outcome, DASH at one year, will be corrected for age and assessed using an analysis of co-variance (ANCOVA). Trends in DASH scores among the different time points will be assessed using a repeated measures ANOVA. The secondary outcomes; PRWE, quality of life (QoL SF-36), pain as indicated on a Visual Analogue Scale (VAS) and Range of Motion (ROM) will be analysed in a similar manner. The radiological outcome, number of conversions and complication rate will be determined using either a Fisher Exact of a Chi square test, depending on the order of magnitude of the results. Subgroup analyses with regard to DASH score will be performed for gender and age for each randomisation stratum.

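### Complications are compared with a test that ignores age, although randomisation is stratified by age and the primary analysis is corrected for it: a minor loss of power that an age-stratified test avoids at almost no cost

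*Protocol article*

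**What the plan says.** Three statements in the protocol article bear on this point.

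- **Randomisation:** "patients will be randomised into three strata according to age: 18-30, 31-60 and >60 years using a block randomisation".
- **Statistical analysis, primary outcome:** "The primary outcome, DASH at one year, will be corrected for age and assessed using an analysis of co-variance (ANCOVA"). PRWE, SF-36, VAS and range of motion follow the same approach.
- **Statistical analysis, binary outcomes:** for radiological outcome, conversions and complications, the "complication rate will be determined using either a Fisher Exact of a Chi square test, depending on the order of magnitude of the results". No stratification or age term is named, and no number marks the change from one test to the other.

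Under Secondary outcomes, the list begins "Complications such as: loss of reduction, fracture malunion or non-union" and goes on to infection, tendon, nerve and pain-syndrome events. Under Sample size, "45 patients in each arm will be included". That section plans for DASH only and gives no complication rate, effect or power.

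**The concern.** The design treats age as important: it governs the allocation, and the primary analysis adjusts for it. The complication comparison leaves it out. Blocking within age bands makes the arms more alike in age than simple randomisation would. A crude 2x2 test does not credit this. It sets its standard error as if the age mix could still differ by chance, so when age predicts complications its real level falls below 5% and power falls with it.

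Complications are the harm to set against any DASH gain from surgery. With 90 patients that comparison has little power to spare, so it matters whether the loss is large or small.

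**Working it through.** **1. Inputs and the plan's own figure.** The only planned calculation is for DASH: the control mean "is 19 with a standard deviation (SD) of 18", a difference of 15 points, and "at α = 0.05% and a power of 90%, with an estimated lost to follow-up of 10" per cent. Reading alpha as 5% two-sided, n = 2 × (1.960 + 1.282)² × 18² / 15² = 30.26 per arm. Multiplied by 1.1 this is 33.3, which matches the stated 33 per arm (66 in total). No figure for complications exists to reproduce. Only the 45 per arm and the three bands come from the article. **All complication risks, odds ratios and stratum sizes below are assumptions.**

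**2. Why the crude test is conservative.** With n_k patients per arm in band k, both tests use essentially the same numerator: observed minus expected events in one arm. They differ in the variance. Under no treatment effect:

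- stratified variance = Σ n_k p_k(1 − p_k)/2
- crude variance = n p(1 − p)/2, where p is the overall risk

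Take 5/20/20 patients per arm and risks of 5/20/50% in the three bands:

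- stratified: 0.119 + 1.600 + 2.500 = 4.219
- overall risk: (0.25 + 4 + 10)/45 = 0.3167; crude: 45 × 0.3167 × 0.6833/2 = 4.869
- ratio: 4.219/4.869 = 0.867, square root 0.931

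The crude test then behaves as if its critical value were 1.96/0.931 = 2.11, a real two-sided level of about 3.5%. Simulations over several risk patterns put crude chi-square at 3.7 to 5.8% and stratified CMH at 4.6 to 5.2%.

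**3. Power under the usual switch.** The switch is taken as Fisher if any expected count is below 5, which is an assumption. There are 90 patients, split 10/40/40 over the bands.

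| Control risks by band | Odds ratio | Switch | CMH | Gain |
|---|---|---|---|---|
| 5/15/35% | 0.35 | 39.2% | 40.4% | 1.2 |
| 5/20/50% | 0.35 | 46.9% | 49.7% | 2.8 |
| 2/5/10% | 3 | 32.3% | 35.5% | 3.2 |

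A second set of runs gave gains of 1.2, 2.8 and 3.4 points, with Fisher selected in 5%, 0.1% and 31% of runs. In the third row crude chi-square alone reaches about 37% and CMH about 36%, so that gain comes from avoiding Fisher and not from the strata.

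**4. How much depends on age.** Crude chi-square against CMH without continuity correction, 6/20/19 patients per arm, 40,000 runs:

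| Age effect | Overall risks | Chi-square | CMH | Gain |
|---|---|---|---|---|
| none | 10% v 31% | 72.1% | 70.6% | −1.5 |
| none | 20% v 43% | 66.7% | 65.7% | −1.0 |
| none | 30% v 60% | 81.7% | 81.6% | −0.1 |
| odds ratio about 4.5 per band | 19% v 48% | 86.7% | 89.3% | about 3 |
| odds ratio about 4.5 per band | 32% v 59% | 75.5% | 82.6% | about 7 |
| odds ratio about 4.5 per band | 42% v 67% | 65.0% | 74.2% | about 9 |

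At an extreme odds ratio of about 12 per band the gain is 16 to 22 points. A separate strongly prognostic scenario gave 47.7% (switch) against 55.0% (CMH), a gain of 7.3 points, with real levels of 2.4% (crude) and 5.1% (CMH).

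**5. False positives.** Exact enumeration of all 2x2 tables at 45 per arm, maximum over event rates up to 50%: Fisher 3.2%, chi-square 6.0%, the usual switch 5.4%, always taking the smaller p-value 6.0%. At 40 per arm, roughly what 10% loss leaves, the last two are 5.7% and 5.9%.

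**The case against.** **A reader might infer a loss of 10 to 14 points of power.** Fisher against chi-square can show such a gap: at 10% v 30% the exact powers are 57.5% and 69.4%, a difference of 11.9. But that is Fisher's conservatism, not the missing strata, and it shrinks to 81.8 − 75.8 = 6 points at 30% v 60%. The article does not prescribe Fisher throughout. Under the usual switch, power at 10% v 30% is 69.3%, almost the chi-square figure. Loss of reduction counts as a complication, and the Background puts redisplacement in cast at up to 60%, so events may well be too common for Fisher to be chosen.

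**A reader might also infer that the error rate is left to the analyst.** The documents do not support this. Choosing between these tests by the size of the counts is common practice, and even always taking the smaller p-value gives at most about 6%. Ignoring balanced strata lowers the level; it does not raise it.

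**The strongest case for leaving the text alone** is that a crude test of an unpowered secondary outcome is valid, and that a journal article may leave the switch point to an analysis plan that is not shown. Much of this stands. The missing threshold is therefore not the finding, and the severity is low. What remains is that the article does name the tests, and the named tests drop the factor used in allocation and in the primary model.

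A fallback to an exact stratified test is itself a switch on counts. That is acceptable only if it is set in advance on the pooled count.

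**Conclusion.** The point holds as a minor improvement. The complication comparison is unstratified in a trial stratified by age. If age predicts complications, the comparison is conservative and loses about 1 to 3 points of power under the usual switch. The loss is about 7 points or more when age is strongly prognostic (3 to 9 at an odds ratio of about 4.5 per band). If age has no effect, nothing is lost and crude chi-square is ahead by up to 1.5 points.

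These sizes rest on assumed risks, effects, stratum sizes and switch rule; the article supplies none of them. There is no material inflation of type I error, and the primary conclusion on DASH is not affected.

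**What to change.** Take complications out of the present sentence and write, for example: *The number of patients with at least one complication will be compared between allocated groups with a Cochran-Mantel-Haenszel test, without continuity correction, stratified by the three age bands used at randomisation. The age-stratified risk difference will be reported with its 95% confidence interval. If the total number of patients with an event, both arms pooled, is below a number fixed here, the exact stratified test will be used instead.* This replaces the clause that lets the size of the results decide. The trial team should set the number before any comparison by arm; fewer than five in total is one option.

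State that no continuity correction is applied. With the correction, CMH power at 20% v 43% and no age effect falls to 56.6%, against 66.7% for crude chi-square, which would cost more than stratifying usually gains.

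The cost is a few sentences, with no new data and no extra patients. The only statistical price is at most about 1 to 2 points of power against crude chi-square if age turns out not to be prognostic.

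### The DASH subgroup sentence sets analyses by gender and for each age stratum but names no comparison of the treatment effect between subgroups

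*Protocol article*

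**What the plan says.** The subgroup plan is one sentence in the Statistical analysis section: "Subgroup analyses with regard to DASH score will be performed for gender and age for each randomisation stratum". The strata are set in the Randomisation section: "patients will be randomised into three strata according to age: 18-30, 31-60 and >60 years using a block randomisation".

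The same Statistical analysis section names a method for the other analyses: ANCOVA corrected for age for the one-year DASH, repeated measures ANOVA for trends, and Fisher's exact or chi-square tests for radiological outcome, conversions and complications. For the subgroups it gives the outcome, the two factors and the stratum as the unit. It gives no model, no comparison between subgroups and no statement of their status.

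The Sample size section deals with the overall comparison only: "we would require 66 patients in total and 33 per treatment arm", then raised so that "45 patients in each arm will be included". No subgroup size or subgroup power is given.

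**The concern.** The most natural reading of the sentence is one analysis per age stratum, plus analyses by gender. A result within a stratum answers whether the arms differ there. It does not answer whether the effect in that stratum differs from the effect in another. With small strata, some will reach significance and others will not, even when the effect is the same in all, and the pattern will also follow stratum size.

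This matters here because the Background describes an earlier trial in patients of 65 and over that found no significant difference in wrist function at six and twelve months. It then presents this trial as the one covering all ages. Readers therefore have a reason to look at the age strata, and a chance pattern could be reported as plating working only at some ages or only in one gender.

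The sentence can also be read in two ways: gender and age separately (two plus three analyses), or gender within each age stratum (six cells).

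**Working it through.** **Inputs from the Sample size section.** Control mean and SD: the one-year DASH after cast treatment "is 19 with a standard deviation (SD) of 18". Assumed effect: 15 points. Alpha, power and loss: "at α = 0.05% and a power of 90%, with an estimated lost to follow-up of 10"%. Enrolment: 45 per arm.

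**Assumptions.** Two-sided tests at 5%, because sidedness is not stated and alpha is printed as 0.05%. Subgroup sizes are not given, so a range is shown. Arms are balanced within subgroups, and SD 18 applies in each, without any gain from covariates.

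**1. The plan's own figure.** n per arm = (1.960 + 1.282)² × 2 × 18² / 15² = 10.51 × 2.88 = 30.3. For 10% loss, 30.3 / 0.9 = 33.6, or 30.3 × 1.1 = 33.3. The stated 33 per arm is reproduced to within one patient per arm. Alpha taken literally as 0.0005 would need 66 per arm before loss, so 5% is evidently what was used. With 45 per arm the overall comparison has 98% power, and 96% after 10% loss (normal approximation).

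**2. Power within a subgroup for the full 15-point effect.** After loss, 90 × 0.9 = 81 patients remain, or 40.5 per arm. Equal genders have 20.25 per arm and equal age strata 13.5. The standard error of a difference is 18 × √(2/n), and power comes from the noncentral t distribution.

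| Subgroup | n per arm | Power |
|---|---|---|
| Gender, 50/50 | 20.25 | 73% |
| Gender, 25/75 | 10 and 30.5 | 42% and 89% |
| Age stratum, equal | 13.5 | 55% |
| Age strata, unequal | 5, 18 and 17.5 | 21%, 68% and 67% |
| Gender crossed with age, six equal cells | 6.75 | 29% |

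**3. Chance of mixed significance when the true effect is 15 points everywhere.** Subgroups of one factor do not overlap, so the chance is 1 − (product of the powers) − (product of 1 − power).

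- Gender, 50/50: 1 − 0.734² − 0.266² = 0.39.
- Gender, 25/75: 0.56.
- Age, three equal strata: 1 − 0.548³ − 0.452³ = 0.74.
- Age, strata of 5, 18 and 17.5 per arm: 0.82.
- Six equal crossed cells: 0.87.

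**4. Spread of the estimates under one common effect.** With 13.5 per arm the standard error of each stratum's effect is 18 × √(2/13.5) = 6.9 points. In simulation the gap between the largest and smallest of the three estimates averages about 12 points, and it exceeds 15 points 28% of the time.

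**5. False positives with no effect anywhere.** If each subgroup were tested at 5%, the chance of at least one is 1 − 0.95⁵ = 23% for five tests and 1 − 0.95⁶ = 26% for six. The five-test figure assumes independence and is approximate, because gender and age subsets overlap.

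**6. What an interaction test can do.** For two equal gender groups, the standard error is 18 × √(2/20.25 + 2/20.25) = 8.0 points and the 95% half-width is 1.96 × 8.0 = 15.7. Power is 47% for a 15-point difference in effect and 15% for 7.5 points. For 80% power the difference must be about 22 points (2.80 × 8.0). With a 25/75 gender split, power for 15 points is 37%. Between two age strata of 13.5 per arm, the standard error is 9.8 and power for 15 points is 33%.

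**The case against.** The strongest objection is that the article is a condensed document. It names no test, p-value or decision rule for the subgroups, and nothing in it rules out an interaction term. How subgroup effects are modelled is commonly left to the full protocol or SAP, neither of which is shown. Analysing by stratum could also mean no more than using the three age bands as categories and giving an estimate and interval in each, which the fix below does too. This stands to the following extent. A reader might infer that the trial has no interaction test, or that within-stratum p-values will decide subgroup claims. The article supports neither inference.

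The percentages also depend on subgroup sizes that the article does not give and on separate 5% tests that it does not specify. That is right, and they are presented on that footing. The conclusion does not need an extreme split, because equal strata already give 74%.

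Further, only two factors are named, both in advance, one of them the stratification factor. The aim and hypothesis concern the overall comparison, and no age- or gender-specific claim is planned. The earlier trial in older patients also differed in fracture type and reduction status. All of this limits the harm.

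The objection does not remove the point. The sentence is not silent: it names the stratum as the unit of analysis, while the same section specifies methods for the other analyses. Taken literally, it sets out results that cannot answer the question a subgroup analysis is for.

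**Conclusion.** The point holds as a low-cost improvement to a secondary analysis. The article sets DASH analyses by gender and for each age stratum and names no comparison of effects between subgroups. Done literally as stratum-wise tests, with an identical 15-point effect throughout, they would give mixed significance about 74% of the time over three age strata and about 39% over gender. Those figures rest on equal subgroup sizes after 10% loss, SD 18 and two-sided 5% tests. The unequal splits examined raise them to 82% and 56%.

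A reader might go further and conclude that the trial's main result is at risk. It is not: the primary ANCOVA, the sample size for the overall comparison and the main conclusion are untouched.

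**What to change.** Replace the subgroup sentence in the Statistical analysis section with wording such as:

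> Effect modification will be examined by adding treatment-by-gender and treatment-by-age-stratum interaction terms, with their main effects, to the one-year DASH ANCOVA on all patients. The age strata are the three used for randomisation. Treatment effects within subgroups will be shown with 95% confidence intervals and without p-values. These analyses are exploratory.

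This also settles whether gender and age are taken separately or crossed. If the full protocol or SAP already contains such a model, align the sentence with it.

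The cost is a few lines of wording, with no extra patients or data and no change to the primary analysis. The downside is low power for the interaction tests: about 47% for a 15-point difference in effect between equal gender groups, and 33% between two equal age strata. A non-significant interaction would therefore not show that effects are equal, and no subgroup-specific claim can be made.

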### Ethical considerations

This study was approved by the Medical Ethical Review Committee of the Academic Medical Centre of the University of Amsterdam (reference number: project 2012_228).

### Regulation statement

This study will be conducted according to the principles of the Declaration of Helsinki version 59, October 2008 and in accordance with the Medical Research Involving Human Subjects Act (WMO) and other guidelines, regulations and Acts.

### Recruitment and informed consent

Patients diagnosed with a displaced extra-articular distal radius fracture will be approached by the investigators and informed about this trial. Patients will receive an elaborate information sheet and contact details of both the investigator and an independent physician. Possible participants will have a period of reflection of five working days. If a patient decides to participate, written and oral informed consent will be obtained.

### Benefits and risks assessment, group relatedness

The treatment that patients will receive is a component of the standard treatment of care, which currently depends on the surgeon’s preference and the complexity of the fracture. Patients will be asked to return to the hospital for follow up at one, three and six weeks, three months, six months and at twelve months. All visits are part of standard care following a fracture treated in this hospital. During these visits patients will be asked about any complaints and/or complications and physical examination will be performed. The assessment of the range of motion of the wrist will take approximately five minutes. Additional to standard care, patients will be asked to fill out three questionnaires at six weeks, three months, six months and one year. Patients will be asked to fill out a DASH form, rate their pain on a Visual Analogue Scale and give an estimation of the type and quantity of pain medication taken during all visits. This will take approximately ten minutes of their time. The PRWE score and the SF-36 will approximately take another ten minutes each. Subjects could experience mild discomfort during physical examination and testing, but this will be no different from that experienced during physical examination during routine follow-up. X-rays will be taken during every visit of which only the final radiographs at one year are additional to standard care. The burden experienced regarding time spent is difficult to estimate but will most likely not exceed 30 minutes. In the total duration of this study, patients will spend an approximate 150 minutes more. The risks are comparable to those that the standard treatment involves. This comprises the standard risk for undergoing a surgical procedure, including risks related to anaesthesia, neurovascular damage and post-operative wound infection. The risks of plaster immobilisation include redisplacement, malunion, loss of function, carpal tunnel syndrome and complex regional pain syndrome. Close follow up and a protocol of treatment, identical to the standard one, will be applied in every subject. Reduction of risks will be done according to inclusion and exclusion criteria. If complications arise, the treating physician will proportionate the adequate treatment according to the current protocols of treatment based on the published literature.

Subjects can leave the study at any time for any reason if they wish to do so without any consequences. The investigator can decide to withdraw a subject from the study for urgent medical reasons. This study will be terminated prematurely if and when patients experience an amount of discomfort or adverse events that is disproportionate to the benefit of the study and presents too great a risk to the participating study subjects. Since the allocated treatment is part of standard treatment of care, no interim analysis, stopping rules or data monitoring was constructed.

